**Figure 1. f1:**
[figure not shown]
Collaborative care model (CCM) interventions in TIME-HF trial.

Two linked mHealth applications (patient and nurse applications) will be developed exclusively for the trial. The nurses, doctors and patients involved in the study will get customised access to the mHealth application. The mHealth application will allow for real time communication between the patients and the concerned nurses in the study. Nurses will be able to communicate also with the treating physician through the application. The mHealth patient application will be made available in Google Play. During the recruitment, the patient application will be installed in the patient’s phone. The concerned nurse will be able to generate a secure secret code with the help of their mHealth application, which will be essential to formally onboard the patient in the mHealth application.

The patient application will be enabled with options to update risk factors, anxiety levels, depression, and warning signs and symptoms of HF. Further, there will be options to send images, text, and voice messages. Every week the mHealth application will push a weekly survey instrument to the patient, which will cover interval assessments of HF, activities of daily living, and warning signs and symptoms. Based on the severity of the signs and symptoms reported, the application will generate amber and red alerts to the nurses. The nurses will be required to respond to those alerts immediately using their mHealth application based on the severity of the alerts and the reaction time to respond to those alerts will be documented. There will be options to modify the prescription of the patient through the mHealth application. Although the nurses can initiate the prescription change and recommend modifications, it will require approval from the treating physician. Once approved by the treating physician, the new prescription will automatically get updated in the patient application. The patients will be able to download the modified prescription using their mHealth application.

The intervention will consists of three phases (
Figure 2); 1) screening and risk stratification, 2) lifestyle modification support (nutritional education, tobacco and alcohol cessation, exercise or activity planning, daily weight monitoring, assessment of the need for cognitive behavioural therapy, and identification of warning clinical signs) and pharmacologic management, and 3) nurse facilitated and mHealth assisted disease management program, self-care management program, active follow-up and continuous monitoring of clinical conditions of the patient while the patient is away from the hospital settings.

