# Team based collaborative care model, facilitated by mHealth enabled and trained nurses, for management of heart failure with reduced ejection fraction in India (TIME-HF): design and rationale of a parallel group, open label, multi-centric cluster randomised controlled trial

**DOI:** 10.12688/wellcomeopenres.19196.2

**Published:** 2023-07-12

**Keywords:** Heart failure, collaborative care model, mhealth application, cluster randomised controlled trial

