## Methods

### Ethical considerations

The participants will be informed about the study and provided with a detailed information sheet
^
30
^. Trained research nurse appointed by the principal investigator will obtain written informed consent from all study participants. The research study is approved by institutional ethics committee of Sree Chitra Tirunal Institute for Medical Sciences and Technology (SCTIMST) and of the participating centres (SCT/IEC/1691/AUGUST-2021). The study protocol is registered with the clinicaltrials.gov (CTRI/2021/11/037797). All changes in the trial protocol will be informed to the institutional review boards.

All serious adverse events will be reported immediately to the respective ethics committees of the participating centres and the study co-ordinating centre (SCTIMST). The principal investigators (PIs) will have access to the final data set. Public access to the data set after de-identification will be provided upon formal request with necessary permission from the SCTIMST ethics committee after three years from the date of completion of the study.

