Caregivers of patients with HF	In-depth interview Total 10–12 IDIs	● Perceptions and behaviours on clinical management, lifestyle, and self-care ● Feedback on proposed intervention components and methods ● Gauge caregivers’ interest and acceptability
Physicians Nurses Dieticians Physiotherapists	In-depth interview 10–12 interviews in each category (30–36 total interviews)	● Perceived quality of HF care ● Perceived patient barriers and facilitators to delivery of care, lifestyle change, and self-care ● Gauge feasibility of planned intervention components

**
*Collaborative care model intervention (Aim 2)*
**

A parallel group cluster RCT of more than 1500 adult HF patients with reduced ejection fraction from 22 units in India
^
36
^ will be used to address Aim 2. Each participating unit will be randomly assigned to one of two arms: 1) those delivering a comprehensive CCM (intervention) or 2) those delivering standard of care (usual care).

The selected hospitals will be independent units with dedicated staff employed at each site for recruitment and follow-up of patients included in the trial. The site teams will have similar compositions in terms of clinical roles.

Cluster eligibility criteria: Eligible units will include HF centres of major hospitals from the national heart failure registry or Kerala heart failure registry that serve ≥80 new patients in six-months and consented to the randomisation plan. All HF patients will also be required to provide individual consent to participate in the study.

Patient eligibility criteria and randomisation: Potential participants must meet the standard definition of HF
^
37
^ (HF with reduced ejection fraction of <40%) based on echocardiography to be eligible to enter the study. Consecutive patients will be recruited from the participating centres. Eligible units will be randomised at one time point, prior to trial implementation. The allocation ratio will be 1:1. Randomisation procedures will not be blocked, restricted, or matched. We will use computer generated random numbers to allocate half of the units to each arm of the study.

*Duration of treatment period and follow-up*

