We will conduct a rolling recruitment over a period of six-twelve months. Each patient in the study will be followed-up for a period of two years from the date of recruitment. The first follow-up visit in the intervention arm will be conducted on the seventh day. Additional two follow-up visits for clinical status occurs at an interval of three-months. Participants are subsequently seen no less than every six months. Regardless of the treatment group assigned, we will follow-up all study participants in this manner (assessment at 7-th day will be only in the intervention arm) until study completion.

*Measurements in the study*

A structured questionnaire
^
38,
39
^ will be administered by trained research nurse to collect relevant data at baseline, and every three months until two years from baseline. At these visits, interval assessments of HF and angina symptom status, current use of medications, and clinical endpoint data including hospitalisations and procedures since the previous visit will be documented (
Table 2). The baseline questionnaire includes assessments of demographic and socio-economic variables, general health status, aetiology, history and risk factors, diet pattern, physical activity, tobacco, and alcohol consumption, quality of life, and six minutes walking distance. Depression and anxiety scores will be collected from each participant by using Patient Health Questionnaire- 9 (PHQ-9)
^
40
^ and Generalized Anxiety Disorder Questionnaire (GAD-7) at baseline and during follow-up visits
^
41
^. Medication adherence will be measured using four item Morisky Green Levine medication adherence scale during the follow-up visits
^
42
^. The follow-up study questionnaire will also assess the patient satisfaction in quality of care, and family support.

**Table 2. T2:** Study measurements in TIME-HF.

Study measurements	Method/Instrument
Blood pressure in mmHg	Electronic BP monitor
Height in cm	Stadiometer
Weight in kg	Digital weighing scale
Waist circumference in inches	Non elastic measuring tapes
Etiology and risk factors	Details of the etiology and risk factors using a questionnaire
Investigations	Blood reports, ECHO, ECG reports
Current Medication	Details of all medications the patient was taking at the time of contact
Depression	PHQ-9 ^ 40 ^
Anxiety	GAD-7 ^ 41 ^

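### Units are randomised before patients are recruited, and only intervention sites install an app on the patient's phone at recruitment, so the arms can enrol different patients and DAOH can be biased

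*Protocol article*

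**What the plan says.** The title calls the trial a "design and rationale of a parallel group, open label, multi-centric cluster randomised controlled trial". Under Collaborative care model intervention (Aim 2), the order of events is given: "Eligible units will be randomised at one time point, prior to trial implementation". Enrolment comes later (Duration of treatment period and follow-up): "We will conduct a rolling recruitment over a period of six-twelve months".

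The hospitals are described as "independent units with dedicated staff employed at each site for recruitment and follow-up of patients included in the trial". Consent is individual: "All HF patients will also be required to provide individual consent to participate in the study". Under Ethical considerations: "Trained research nurse appointed by the principal investigator will obtain written informed consent from all study participants". No recruiter blinded to allocation is described, nor any identification of patients before allocation.

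The stated patient criterion, the same for both arms, is heart failure with an ejection fraction below 40% on echocardiography. On how patients are taken in: "Consecutive patients will be recruited from the participating centres".

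Study intervention overview gives collaborative care (CCM) to intervention units only. The text after Figure 1 says the patient app comes from Google Play, and then: "During the recruitment, the patient application will be installed in the patient’s phone". A code generated by the nurse is needed to bring the patient into the app. The usual-care paragraph has no corresponding step.

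The Data analysis plan provides for intention to treat, a baseline comparison by arm, and a Poisson model with robust variance for DAOH. It names no baseline covariates for that model.

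**The concern.** In a cluster trial, randomising hospitals balances hospitals. It does not protect the comparison of patients if they are identified and consented afterwards by people who can know the arm. Here there is also a concrete step that differs by arm: a recruit at an intervention hospital is expected to have a phone on which the app can be installed, and a recruit at a usual-care hospital is not.

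Patients without such a phone may well be older, poorer or frailer. If intervention sites enrol fewer of them, the arms differ in prognosis before any treatment effect. Intention to treat and cluster-robust standard errors work only on the patients who were enrolled, so neither corrects this. A positive DAOH result could then be challenged as patient selection.

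**Working it through.** **Does the mechanism follow from the text?** Four statements combine: allocation precedes recruitment, the trial is open label, site staff recruit and consent, and one arm alone has a device-dependent step during recruitment. A patient without a suitable phone cannot be recruited at an intervention site in the way the article describes, and no alternative is given. At a usual-care site the same patient meets no obstacle.

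**Do sites have room to select?** Eligible units see at least 80 new patients in six months, and each is to recruit 70. Over six to twelve months a unit of minimum size sees 80 to 160 new patients for 70 places. Not all will have an ejection fraction below 40%, so the margin is smaller than it looks, but larger units have more.

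**Precision of the primary comparison.** Inputs from Trial sample size and power: SD 69 days, 770 per arm, design effect 2.08 (taken as stated).

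- SE of the difference = 69 × √(2 × 2.08 / 770) = 5.07 days.
- Target: 586 − 566 = 20 days, or 3% × 566 = 17.0 days.
- Check against the stated 91% power: the normal approximation with this SE gives 97.6% at 20 days and 91.7% at 17 days. The stated figure fits the 3% reading. That mismatch is a separate matter; both values serve here only as the yardstick.

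**Size of the bias.** The article has no figure for this, so the inputs are assumptions: share p of eligible patients without a suitable phone, 20-40%; their DAOH deficit D, 30-60 days. Let e be the fraction of them missed in the intervention arm, with none missed in usual care. Their share among intervention enrollees is p(1 − e)/(1 − pe), so

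bias = D × [p − p(1 − e)/(1 − pe)].

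- All missed (e = 1): bias = pD, from 0.20 × 30 = 6 days to 0.40 × 60 = 24 days.
- Half missed (e = 0.5), low end: 30 × [0.20 − 0.10/0.90] = 2.7 days.
- Half missed, high end: 60 × [0.40 − 0.20/0.80] = 9 days.

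**Effect on the test.** With no true effect and a bias b, the two-sided 5% test rejects with probability 1 − Φ(1.96 − b/5.07) + Φ(−1.96 − b/5.07).

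| Bias (days) | Type I error |
|---|---|
| 2 | about 7% |
| 5 | about 17% |
| 10 | about 50% |

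**The case against.** The strongest reply is that the article never makes a phone a condition of entry. The sentence on installation belongs to the description of the intervention, the code brings the patient into the app and not into the trial, and all patients at intervention units are to receive CCM-based care, much of which needs no patient phone. This stands as far as it goes. A reader might infer a written smartphone requirement in one arm, and the documents do not support that: it is implied by what happens at recruitment. The missing route for a patient without a phone remains.

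Second, consecutive recruitment applies to both arms and is a genuine safeguard against staff picking patients. It is therefore not established that usual care enrols everyone while intervention sites select. But it does not prevent patients from consenting differently when the arm is known, and it does not say how a consecutive patient without a phone is recruited at an intervention site.

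Third, this is a condensed article. Screening logs and covariate adjustment may stand in the full protocol or SAP, and their absence here is not the finding. The finding is the arm-specific step that the article does state. Age, socio-economic status and frailty are collected at baseline and compared by arm. That comparison can reveal an imbalance but does not correct it. With 22 clusters and unrestricted randomisation, chance imbalance would be hard to tell from recruitment bias.

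Fourth, size and direction rest on assumptions. A 60-day deficit is close to one SD (60/69 = 0.87), and sites or patients might instead favour enrolling sicker patients where extra support is offered. Both points stand and limit the conclusion.

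**Conclusion.** The point holds as a design risk. Recruitment takes place after allocation that staff can know, and one arm has an additional device-dependent step with no stated route around it. Intention to treat, robust variance and a baseline comparison cannot remove the resulting bias.

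It would be tempting to conclude that the trial will overstate DAOH by 6-24 days. The documents do not support that. The range needs both assumed inputs, the loss of every patient without a phone in one arm, and none in the other; with half lost it is about 3-9 days. A bias in favour of the intervention is probable, not certain. What can be said from the article's own figures is that the standard error is about 5 days, so even a bias near the lower part of these ranges would matter for a test aimed at 17-20 days.

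**What to change.** - State that consecutive eligible patients are enrolled in both arms regardless of phone ownership, that intervention patients without a phone receive the other CCM components, and that all are analysed as randomised.
- Record own or household smartphone access at baseline for all remaining enrolments in both arms.
- Report screened, eligible and enrolled counts, with reasons for non-enrolment, by site and arm.
- Prespecify a DAOH analysis adjusted for prognostic baseline variables already collected, such as age, socio-economic status, frailty, KCCQ and six-minute walk distance. This reduces bias from measured differences only.
- For patients already enrolled, use retrospectively collected phone access only descriptively or in a sensitivity analysis. It will be missing for patients who died or were lost, and so missing in relation to DAOH itself.

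The cost is one case report form item, a screening tally, a short amendment, and some intervention patients who do not receive the app. Study status says recruitment had started at submission, so the enrolment statement and baseline item may reach only some patients. The adjusted analysis, and the screening counts where sites have kept records, remain possible either way.

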**Figure 2. f2:**
[figure not shown]
Overview of the study intervention in TIME-HF. RCT-Randomised Controlled Trial, DAOH-Days Alive and Out of Hospital, EHR-Electronic health record.

**
*Evaluate the scalability of proposed intervention model (Aim 3)*
**

*Cost effectiveness and acceptability analyses*

Information for economic analyses will be collected during the trial to obtain detailed resource consumption. A top-down approach will capture implementation costs from a health systems perspective by quantifying the resources deployed. Some of these will be once only activities (e.g., development of a mobile telephone application) but most will be recurring (e.g., nurse hours per year). We will then cost these resources according to unit costs in India. A bottom-up approach will collect patient level out of pocket expenditure and other personal financial losses or gains. It will include human resource costs, doctor visits, laboratory tests, cost of medications, and co-payments for medications. Rates of outpatient (specialty clinic) visits, hospitalisations, and clinical events will also be obtained. Indirect costs (travel, missed work time, and lost productivity) incurred by patients will be estimated using questionnaires that have been used in other South Asian studies
^
54
^.

We will collect qualitative data during the follow-up period. In depth interviews with patients, nurses and clinicians will be conducted to understand the adoption and acceptability of the intervention (
Table 4). Qualitative data collection approaches will be employed for prospective process measure evaluation during the trial. Process measures will include quality of care (patient centredness, safety, equity, access, and timeliness), and individual, organisational and system factors influencing effective roll-out of the intervention (causal mechanisms and contextual factors, further barriers and facilitators and motivators). The acceptability of the trial intervention among providers and patients, the feasibility of integrating and sustaining the program in the existing health care system will be also assessed. Additionally, by using a close-out questionnaire, we will also ask patients to self-report their compliance to individual elements of the intervention. Data from follow-up visits questionnaire will also capture key quality indicators (
Table 5). The key domains of quality will include access, timeliness, safety, patient centredness, and equity. We will describe fidelity to the intervention package components, types of changes made by healthcare organisations, how the changes were implemented, and identify multi-level contextual factors and causal pathways that affect implementation, process, and outcomes. We will use triangulation to integrate close-out questionnaire, follow-up questionnaire and qualitative process outcomes data.

**Table 4. T4:** Qualitative methods to understand the adoption and acceptability of interventions.

Participants	Methods/Number	Topics
Patients with HF both male and female in various age groups	In-depth interview Total 10-12 IDIs	• Quality of care (safety, patient centeredness, equity, access, timeliness) • Satisfaction and adherence to intervention. • Factors contributing to use/refusal of intervention. • Suggestions for modification.
Physicians Nurses, organisation leaders and implementers	In-depth Interviews 10-12 interviews in each category (20- 24 total interviews)	• Quality of care (safety, patient centeredness, equity, access, timeliness) • System related barriers for adoption of intervention. • Barriers at patient level. • Satisfaction and suggestions for modifications.

**Table 5. T5:** Performance indicators in TIME-HF.

Performance indicator	Description
*In-patient measures*	
Evaluation of left ventricular systolic (LVS) function	Proportion of HF patients with LVS function assessed before arrival, during hospitalisation, or is planned after discharge.
Angiotensin-converting enzyme inhibitor (ACEI), or angiotensin receptor blocker (ARB) for left ventricular systolic dysfunction (LVSD)	Proportion of HF patients with LVSD and without both ACEI and ARB contraindications who are prescribed ACEI or ARB at hospital discharge.
Anticoagulant at discharge for HF patients with atrial fibrillation (AF)	Proportion of HF patients with AF and without contraindications who are prescribed warfarin or NOACs at discharge.
Clinical handover	Proportion of HF patients discharged home with written instructions addressing all of the following: activity level, diet, discharge medications, follow-up appointment, weight monitoring, and what to do if symptoms worsen.
Adult smoking cessation advice/counselling	HF patients with a history of smoking cigarettes, who are given smoking cessation advice or counselling during hospital stay.
*Outpatient measures*	
LVS function assessment	Proportion of HF patents with documentation that LVS has been assessed.
Weight measurement	Proportion of patients with measurement of weight at each outpatient visit to assess change in volume status.
Blood pressure measurement	Measurement of patient’s blood pressure and calculation of pulse pressure at each outpatient visit.
Assessment of clinical signs and symptoms of volume overload (excess)	Assessment of clinical symptoms of volume overload at each outpatient visit (e.g., dyspnoea, orthopnoea). Signs include peripheral oedema, rales, hepatomegaly, and ascites. Proportion of patients without hypoperfusion and congestion.
Assessment of activity level	Proportion of patients with evaluation of the impact of HF on activity level at each outpatient visit.
Patient education	Percentage of patients who were provided with patient education on disease management and health behaviour changes during follow-up visits.
Beta-blocker therapy	Prescription of beta-blockers in patients with HF and LVSD. Adherence to Beta- blocker therapy at follow-up visit.
ACEI or ARB therapy for patients with HF who have LVSD	Proportion of patients with prescription of ACEI or ARB for management of outpatients with LVSD. Adherence to ACEI or ARB therapy at follow-up visit.
MRA for patients with HF	Prescription of MRA for management of outpatient with LVSD. Adherence to MRA therapy at follow-up visits.
Warfarin therapy for patients with AF	Proportion of HF patients with chronic/recurrent AF and without contraindications who are adherent to warfarin/NOACs at follow-up.
Assessment of depression	Proportion of patients with assessment for depression

NOACs- Novel oral anticoagulants, MRA- Mineralocorticoid Receptor Antagonists

